### Control arm

As a pragmatic trial investigating image-guided, tumor-focused RT for intermediate- and high-risk prostate cancer, RadTARGET is not overly prescriptive for the control arm. Control arm definitive RT modality, dose, frequency, and administration must be in concordance with RMAS Standards and Guidelines or local institutional standard practice. Image-guided focal boost to MRI-visible disease is allowed and generally expected, but not required. For the control arm, the prostate CTV includes the entire prostate and receives the full prescription dose, corresponding to the relevant allowed fractionation scheme (i.e., *CTV_high* in Table 2). The proximal seminal vesicles may be included at physician discretion and would receive the *CTV_low* dose in Table 2.

### Both arms

For both trial arms, all other CTV and PTV structures should conform to RMAS or local institutional standards and guidelines. NOIs should be delineated per RMAS guidelines or local institutional practice. The urethra must be delineated if a focal tumor boost is delivered. As a pragmatic trial, all plans will be optimized to reflect NOIs constraints of RMAS or local institutional standards & guidelines. RMAS guidelines NOIs constraints for all fractionation schemes are provided in the Supplement. The treating physician must state their intended radiation technique, number of fractions, coverage of lymph nodes, use of adaptive RT, and plan for spacer prior to randomization. Systemic therapy (e.g., ADT) is allowed at discretion of the treating physician, who must state the intended medications and duration prior to randomization (see Supplement).

### Radiation therapy simulation (both arms)

Simulation allows for computer-based optimization of radiation dose delivery to the target tissue and simultaneous dose minimization to surrounding normal tissues. In both arms, simulation with CT and/or MRI is performed by RT-trained MR technologists per clinical routine. The diagnostic MRI +/- PSMA PET/CT are registered to the CT simulation for target delineation. A post-ADT planning MRI close to the date of the simulation is required for patients who began ADT more than 3 weeks prior to simulation. Full or empty bladder protocols are acceptable.

### Radiation therapy planning and delivery (both arms)

RT planning is performed by trained dosimetrists and/or radiation physicists (complying with RMAS guidelines or local institutional practice) and documented in the medical records. Peer review of RT plans by radiation physicists and at least one radiation oncologist is required, as well as contouring of all NOIs within 5 cm of any target volume. All plans must use modern planning and delivery techniques (e.g., VMAT), regardless of fractionation (conventional, hypofractionated, or SBRT). Target dose and/or coverage should be lowered to meet hard NOI dose goals, as needed (dose goals listed in Supplemental Tables 2-4). NOI dose goals may be exceeded in the patient’s interests at discretion of the treating physician. RT delivery is performed by trained RT therapists. A comparison of standard and tumor-focused plans for an example patient is shown in Fig. 2.

**Fig. 2 f0010:**
[figure not shown]
Comparison of standard dose and tumor-focused radiotherapy (RT) plans on computed tomography (CT) images for the RadTARGET trial. Magnetic resonance images (MRI) are used to localize the tumor for intensified treatment dose at the GTV (and for prostate and urethra contours). Restriction spectrum imaging restriction score (RSIrs) maps (overlaid on T2-weighted images) help radiation oncologists target the tumor. In the control arm, standard RT dose is applied to the entire prostate (with a uniform margin of 4 mm). Image-guided focal boost to MRI-visible disease is allowed and generally expected. In the experimental arm, the dose is increased at the tumor (with a uniform margin of 5 mm, limited to within the prostate) and decreased outside of the tumor. The patient shown was treated with Stereotactic Body Radiation Therapy (SBRT). Abbreviations: GTV = gross tumor volume, Gy = gray.

### Study endpoints

•Primary Endpoint: physician-reported, all-attribution acute GI or GU grade ≥2 adverse events. Adverse events will be defined using CTCAE version 5.0 grading. This study will evaluate the relative merits of standard dose RT and image-guided tumor-focused RT in terms of safety, patient-reported outcomes, and oncologic efficacy.•Secondary Endpoints:oAcute radiation-attribution GU/GI grade ≥2 adverse events.oAcute radiation-attribution grade ≥2 GU adverse events, other than alpha blockers.oAcute any-attribution and radiation-attribution grade ≥3 GU/GI adverse events.oLate any attribution and radiation-attribution grade ≥2 and grade ≥3 GU/GI adverse events.oPatient-reported urinary and bowel quality of life, defined as a decrease of 7 points and 6 points on the irritative/obstructive and bowel domains, respectively, of EPIC-26 at 3 months, 6 months, 12, 18, and 24 months after completion of RT.oBiochemical recurrence free survival at 5 years, defined as the percentage of participants alive and without biochemical at 5 years after completion of RT.oLocal failure at 5 years, defined as the percentage of participants with intra-prostatic recurrence (as assessed by MRI and/or PSMA PET/CT or via confirmatory biopsy after biochemical recurrence) at 5 years after completion of RT.oDistant-metastasis-free survival at 5 years, defined as absence of local or regional lymph node recurrence (as confirmed on imaging including PSMA PET/CT and mpMRI) at 5 years after completion of RT.oOverall survival at 5 years, defined as the percentage of patients alive at 5 years after completion of RT.

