## Design

RadTARGET is a phase II, two-arm, randomized clinical trial evaluating tumor-focused RT versus standard-dose RT. Evaluation will be performed in terms of physician-reported adverse events, patient-reported safety, and oncologic outcomes. Participants will undergo RT for intermediate- or high-risk localized PC (Fig. 1). A dynamic allocation procedure is used to assign participants in a 1:1 ratio to receive either standard-dose RT or image-guided, tumor-focused RT. To minimize biased clinical decision-making based on randomization, treating physicians will declare the participant’s treatment plan prior to randomization. Each arm will be balanced for risk group (intermediate/high), fractionation type (stereotactic body RT [SBRT] / non-SBRT), duration of androgen deprivation therapy (ADT; none/short-term/long-term), bladder filling (full/empty), and spacer use (yes/no). The primary objective is to evaluate the relative merits of image-guided, tumor-focused RT vs. standard-dose RT for acute GU/GI adverse events in the setting of definitive RT for intermediate- and high-risk PC. The endpoint will be acute, any-attribution GU/GI grade ≥2 adverse events within 3 months of completing RT, compared between randomized arms. Adverse events will be defined using Common Terminology Criteria for Adverse Events (CTCAE) version 5.0 grading.

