### Statistical analysis

We adopt a statistical approach based on estimating the difference in adverse event rate (proportion of patients experiencing an adverse event) between the two randomized groups by controlling the precision (width) of the associated confidence interval for that difference. The primary endpoint is acute GU or GI grade ≥2 adverse events. We will estimate the absolute difference in adverse event rate between tumor-focused radiotherapy and standard dose radiotherapy using an intention-to-treat (ITT) analysis approach.

The following randomized trials and meta-analyses guide our assumptions for sample size determinations: RTOG 0415, PROFIT, HYPRO, PACE-B, FLAME, Hypo-FLAME, and MIRAGE [2], [4], [13], [27], [28], [29], [30]. From this high-level evidence, we assume the combined GU and/or GI acute adverse event rate is 40%. The MIRAGE trial included 156 participants and found a meaningful difference in acute GU and GI safety when comparing a difference in PTV margin size of 2 mm. We assume that the tumor-focused approach will lead to a similar adverse event reduction via the same mechanism.

We seek to answer whether the tumor-targeted approach reduces the rate of acute GU/GI adverse events. If we assume acute adverse events are reduced from 40% to 25% (absolute rate difference of −15%), we estimate that a sample size of 150 participants (75 in each arm) will yield a one-sided 90% confidence interval (one-sided equivalent to 95% confidence interval for a two-sided test) with 12.4% margin of error. Thus, we expect to have >95% confidence that the true rate difference is non-zero. We expect minimal attrition, but even 10% missing data would have a minimal impact on the margin of error (<1%). If adverse event rates in the standard arm were higher or lower than expected (30–70%), we would still have sufficient power to detect the assumed 15% absolute rate difference.

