All primary and secondary analyses will be conducted with the intention-to-treat principle. All participants will be analyzed according to the group they were randomly assigned to, regardless of compliance with the trial protocol. Patients who did not receive RT treatment will be considered screen failures. The primary endpoints (proportion of patients with acute grade ≥2 GU or GI adverse events) will be compared across the two randomized groups using a stratified Cochran–Mantel–Haenszel test with the stratification factors listed above. We will also repeat the analysis using a non-stratified Fisher’s exact test.

Secondarily, we will develop a multivariable logistic regression model with binary dependent variable (presence or absence of acute grade ≥2 GU or GI adverse events) and independent variables to include randomization group and all covariates listed above. This will allow us to estimate the effects of each variable, with bootstrap 95% confidence intervals. The primary and secondary analyses above will be repeated in the following subgroups: (1) self-reported race/ethnicity, and (2) age <65 vs. ≥65 years. This is in addition to subgroup analyses within the stratification groupings for randomization. Description of translational sub-studies provided in the Supplement.

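### The patient-reported endpoint is fixed as a yes/no EPIC-26 drop; a baseline-adjusted analysis of the continuous score would recover precision from data the endpoint already requires

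*Protocol article*

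**What the plan says.** Under Study endpoints, the protocol article lists the EPIC-26 endpoint among the secondary endpoints: "defined as a decrease of 7 points and 6 points on the irritative/obstructive and bowel domains, respectively, of EPIC-26". Five assessment times follow, from 3 to 24 months after the end of radiotherapy. No mean-score endpoint is listed beside it. The word decrease implies a baseline score. The article does not describe the baseline visit and leaves data collection to a supplement that is not shown.

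Under Statistical analysis, one regression model is described. Its outcome is the occurrence of an acute grade 2 or higher GU or GI event, and its predictors are given as "independent variables to include randomization group and all covariates listed above". The list referred to is the set of balancing factors under Design: "Each arm will be balanced for risk group (intermediate/high), fractionation type (stereotactic body RT [SBRT] / non-SBRT), duration of androgen deprivation therapy". Two further factors complete that list, namely "bladder filling (full/empty), and spacer use (yes/no"). None of these measures urinary or bowel function before treatment. The model is introduced as a secondary analysis. The primary comparison is made "using a stratified Cochran–Mantel–Haenszel test with the stratification factors listed above".

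**The concern.** Design and Study endpoints both name patient-reported outcomes as one of the bases on which the two strategies will be judged, and EPIC-26 is the only listed instrument completed by the patient. Two domains at five visits give ten yes/no comparisons with 75 patients per arm. A patient who falls 8 points counts the same as one who falls 30, and a patient who falls 5 counts the same as one who improves.

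The trial is built around the width of a confidence interval, so precision is its own yardstick. A true difference in urinary or bowel function could be estimated too imprecisely to inform the phase III decision, although the same questionnaires would support a tighter estimate.

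**Working it through.** **Inputs from the article.** 150 patients, 75 per arm; primary event rates of 40% and 25%; thresholds of 7 and 6 points; five visits.

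**Inputs that must be assumed.** The share of patients crossing the threshold (p), the distribution of scores, the correlation between baseline and follow-up (r), and how strongly baseline score predicts acute adverse events. The article gives none of these.

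**1. The plan's own figure.** The article states no precision for EPIC-26. Its margin of error for the primary endpoint is 12.4%, which reproduces: 1.645 × √(0.40×0.60/75 + 0.25×0.75/75) = 1.645 × √(0.0032 + 0.0025) = 12.42%. It is the baseline for step 5.

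**2. Yes/no change against mean change, normal scores.** The retained information for a small shift is φ(z_p)² / [p(1−p)].

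| p crossing threshold | Retained | Lost | 150 patients count as |
|---|---|---|---|
| 20% | 0.490 | 51% | 73 |
| 30% | 0.576 | 42% | 86 |
| 40% | 0.622 | 38% | 93 |
| 50% | 0.637 | 36% | 95 |

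At p = 10% the loss would reach 66%.

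In power terms, take an assumed true difference of 0.4 SD and 40% control responders. The experimental responder rate is Φ(−0.253 − 0.4) = 25.7%. With 75 per arm and two-sided 5%, power is 69% for mean change and 46% for the yes/no endpoint.

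**3. The same with scores capped at 100.** EPIC-26 scores are bounded, so normality may overstate the loss. Simulations assumed baseline mean 85 (SD 14) or 92 (SD 12) before capping, r of 0.4 or 0.6, and mean drops of 9 and 4 points in the two arms. Responder rates were 51–57% in control and 32–42% in experimental. The loss against mean change was 26–31%.

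**4. Against a baseline-adjusted analysis.** With equal variances, the change score has variance 2σ²(1−r) and the baseline-adjusted score σ²(1−r²), a ratio of (1+r)/2 in favour of adjustment. At r = 0.5 this is 0.75. The yes/no endpoint then retains 0.622 × 0.75 = 0.467 at p = 40%, a loss of 53%. Over r = 0.3–0.7 and p = 25–50% the normal-theory loss is 46–65%. In the capped simulations it is 36–47%.

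**5. Baseline scores in the acute adverse-event model.** If baseline function explained a share R² of the outcome variance, the margin of error would scale by √(1−R²):

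| Assumed R² | Margin of error |
|---|---|
| 0 | 12.42% |
| 0.02 | 12.29% |
| 0.05 | 12.10% |
| 0.10 | 11.78% |

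The gain is about 0.1–0.6 percentage points, and it applies only to a covariate-adjusted risk difference. The logistic model by itself yields a conditional odds ratio.

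On the cost side, expected events are 75×0.40 + 75×0.25 = 48.75, about 49. The model already has about 7 terms: arm, risk group, fractionation, two for ADT duration, bladder filling and spacer. Two more terms take events per term from 49/7 = 7.0 to 49/9 = 5.4.

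**The case against.** The best defence is that a responder proportion is a legitimate measure that clinicians can interpret, and that it matches the trial's general approach of comparing the proportions of patients affected. EPIC-26 is one of several secondary endpoints and does not drive the sample size. The article is also a condensed account, so the EPIC-26 model may well be in an analysis plan that is not shown.

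Most of this stands. It is why the proportions should be kept and why the point is about efficiency. It does not remove the point, because the article fixes the endpoint itself as a threshold, and an analysis plan would normally specify how to analyse that endpoint.

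A reader might infer four stronger things that the documents do not support:

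- **That baseline EPIC-26 is omitted from every model.** Only one model is described, and it concerns acute adverse events. The absence of an EPIC-26 model from a condensed article is no finding, and baseline already enters the endpoint through the subtraction.
- **That regression to the mean distorts the result.** Under 1:1 randomisation it affects both arms alike in expectation, so only precision is at issue.
- **That the primary comparison loses power.** Adding terms to the secondary logistic model leaves the stratified primary test as it is.
- **That the covariate is free.** It adds two terms to a model with about 49 expected events and needs a rule for missing baseline scores.

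**Conclusion.** The point holds as a loss of efficiency on a secondary endpoint. Nothing here is a contradiction or a bias. The size is roughly 26–50% of the information against mean change for 20–50% responders, and more against a baseline-adjusted analysis. A single figure such as 40% should not be quoted as fact: it fits a normal change score with about 30–45% of patients crossing the threshold, and capped scores give less. All these ranges depend on the assumed distribution, responder share and baseline correlation.

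The change is worth making because the endpoint already requires the data. The covariate suggestion for the acute adverse-event model is optional. Its value depends on an unshown prognostic strength and is small at modest R².

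**What to change.** Make the main EPIC-26 analysis a repeated-measures model of each continuous domain score (urinary irritative/obstructive and bowel) at 3, 6, 12, 18 and 24 months, adjusted for the baseline score and the balancing factors, and report the arm difference with its interval at each visit. Keep the proportions with a 7- or 6-point drop as supportive results. Fix this before outcome data are seen, since a later switch would look data-driven.

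Optionally, add the baseline irritative/obstructive and bowel scores to the secondary logistic model, with a stated rule for a missing baseline score. The primary test stays unchanged.

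The cost is analysis wording only, with no added patients, visits or questionnaires, provided that baseline EPIC-26 is collected as the definition implies.

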### Statistical analysis

We adopt a statistical approach based on estimating the difference in adverse event rate (proportion of patients experiencing an adverse event) between the two randomized groups by controlling the precision (width) of the associated confidence interval for that difference. The primary endpoint is acute GU or GI grade ≥2 adverse events. We will estimate the absolute difference in adverse event rate between tumor-focused radiotherapy and standard dose radiotherapy using an intention-to-treat (ITT) analysis approach.

The following randomized trials and meta-analyses guide our assumptions for sample size determinations: RTOG 0415, PROFIT, HYPRO, PACE-B, FLAME, Hypo-FLAME, and MIRAGE [2], [4], [13], [27], [28], [29], [30]. From this high-level evidence, we assume the combined GU and/or GI acute adverse event rate is 40%. The MIRAGE trial included 156 participants and found a meaningful difference in acute GU and GI safety when comparing a difference in PTV margin size of 2 mm. We assume that the tumor-focused approach will lead to a similar adverse event reduction via the same mechanism.

We seek to answer whether the tumor-targeted approach reduces the rate of acute GU/GI adverse events. If we assume acute adverse events are reduced from 40% to 25% (absolute rate difference of −15%), we estimate that a sample size of 150 participants (75 in each arm) will yield a one-sided 90% confidence interval (one-sided equivalent to 95% confidence interval for a two-sided test) with 12.4% margin of error. Thus, we expect to have >95% confidence that the true rate difference is non-zero. We expect minimal attrition, but even 10% missing data would have a minimal impact on the margin of error (<1%). If adverse event rates in the standard arm were higher or lower than expected (30–70%), we would still have sufficient power to detect the assumed 15% absolute rate difference.

All primary and secondary analyses will be conducted with the intention-to-treat principle. All participants will be analyzed according to the group they were randomly assigned to, regardless of compliance with the trial protocol. Patients who did not receive RT treatment will be considered screen failures. The primary endpoints (proportion of patients with acute grade ≥2 GU or GI adverse events) will be compared across the two randomized groups using a stratified Cochran–Mantel–Haenszel test with the stratification factors listed above. We will also repeat the analysis using a non-stratified Fisher’s exact test.

Secondarily, we will develop a multivariable logistic regression model with binary dependent variable (presence or absence of acute grade ≥2 GU or GI adverse events) and independent variables to include randomization group and all covariates listed above. This will allow us to estimate the effects of each variable, with bootstrap 95% confidence intervals. The primary and secondary analyses above will be repeated in the following subgroups: (1) self-reported race/ethnicity, and (2) age <65 vs. ≥65 years. This is in addition to subgroup analyses within the stratification groupings for randomization. Description of translational sub-studies provided in the Supplement.

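### The 12.4-point margin that supports n=150 is a two-sided 90% half-width (a one-sided 95% bound), not the one-sided 90% or two-sided 95% interval it is labelled as

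*Protocol article*

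**What the plan says.** The Statistical analysis section of the protocol article sizes the trial on the width of the confidence interval for the difference in acute grade ≥2 GU/GI event rates. The steps are:

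- Planning rates: "If we assume acute adverse events are reduced from 40% to 25% (absolute rate difference of −15" points.
- Size: "a sample size of 150 participants (75 in each arm"), consistent with the Design section, which says the trial will "assign participants in a 1:1 ratio to receive either standard-dose RT or image-guided, tumor-focused RT".
- Level of the interval and resulting precision: "one-sided 90% confidence interval (one-sided equivalent to 95% confidence interval for a two-sided test) with 12.4% margin of error".
- Inference drawn from it: "Thus, we expect to have >95% confidence that the true rate difference is non-zero".
- Robustness to missing outcomes: "even 10% missing data would have a minimal impact on the margin of error (<1" point). The article expects little attrition and offers 10% as a stress case.

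**The concern.** The sentence that sets the precision names two confidence levels, treats them as the same, and attaches one margin to both. A one-sided 90% interval uses the same normal quantile as a two-sided 80% interval. A two-sided 95% interval uses the same quantile as a one-sided 97.5% bound. The two cannot share a margin, so at least one label had to be wrong whatever the data.

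The level matters because the trial is sized on precision, and this margin is the only sample size calculation the article shows. The next sentence then uses the margin to claim more than 95% confidence that the difference is not zero, which is a two-sided statement. If the margin belongs to a lower two-sided level, a reader is led to think that the planning result clears zero by about 2.6 points at two-sided 95%, when the clearance at that level is much smaller.

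**Working it through.** **Inputs** (Statistical analysis section; 1:1 allocation from Design): control rate 0.40, experimental rate 0.25, 75 per arm, planning difference −15 points.

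**Standard error** (unpooled):

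SE = √(0.40×0.60/75 + 0.25×0.75/75) = √(0.0032 + 0.0025) = √0.0057 = 0.0755, or 7.55 points.

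**Reproducing the article's figure.** 1.645 × 7.55 = 12.4 points, so the printed number is reproduced. Working backwards, 12.4/7.55 gives z = 1.642, which is a one-sided level of 95.0% or a two-sided level of 89.9%.

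**Margin at each level, with the limits at an observed −15 points:**

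| Level | z | Margin (points) | Limits (points) |
|---|---|---|---|
| One-sided 90% (= two-sided 80%) | 1.282 | 9.7 | upper bound −5.3 |
| One-sided 95% (= two-sided 90%) | 1.645 | 12.4 | −27.4 to −2.6 |
| Two-sided 95% (= one-sided 97.5%) | 1.960 | 14.8 | −29.8 to −0.2 |

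The article's labels are those of the first and third rows; its number is in the second.

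**Could another interval method give 12.4 at a labelled level?** No.

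| Method | One-sided 90% | Two-sided 95% |
|---|---|---|
| Wald, pooled variance | 9.8 | 15.0 |
| Wald, continuity-corrected | 11.0 | 16.1 |
| Agresti–Caffo | 9.6 | 14.7 |
| Newcombe (the two sides differ) | 9.4–9.8 | 14.1–15.0 |

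**The conclusion about a non-zero difference.** If the observed difference is exactly −15 points, z = 0.15/0.0755 = 1.987. That is 97.7% one-sided confidence and 95.3% two-sided (p = 0.047 unpooled; 0.0499 with pooled variance). The two-sided result depends on the method. With the continuity correction the margin of 16.1 exceeds 15. Because 25% of 75 is 18.75, the nearest whole counts are 18 and 19: Fisher's exact test gives two-sided p = 0.054 for 30/75 against 18/75 and p = 0.081 for 30/75 against 19/75.

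**The 10% stress case.** 75 × 0.9 = 67.5 per arm, so SE = √(0.4275/67.5) = 0.0796.

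- At z = 1.645 the margin is 13.1 points, an increase of 0.67. Zero is still excluded at −15.
- At z = 1.960 the margin is 15.6 points, an increase of 0.80. The interval now includes zero at −15.

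The increase is below one point at both levels, so the article's statement about it is right.

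**The case against.** The best defence is that this is a slip of words: one-sided and two-sided were probably exchanged. The number 12.4 is correct at z = 1.645, the question is directional (does the tumor-focused approach reduce events), and a one-sided 95% bound suits that question. All of this stands. It explains the error but does not remove it, because the text as written names two other levels and draws a two-sided conclusion.

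Several stronger readings are tempting, and the article does not support them:

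- *That the claim of more than 95% confidence is numerically false.* It is not. At an observed −15 points the inputs give 97.7% one-sided and 95.3% two-sided by the Wald method. The fault is that the claim does not follow from the 12.4 margin and, read two-sidedly, holds only narrowly and not under every method.
- *That the missing-data sentence is wrong.* It is correct at either level. Nor is 10% a planned loss; it is a stress case.
- *That the plan leaves several competing error rates for the primary test.* The article gives no sidedness for the Cochran–Mantel–Haenszel and Fisher tests, but an article commonly leaves this to the full protocol or SAP, which are not shown. The 95% bootstrap intervals belong to a secondary logistic model.
- *That 150 participants rests on this margin alone.* It is the only calculation shown, but the article also points to a cited trial of 156 participants as guiding its assumptions.

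**Conclusion.** The point holds as a mislabelled design figure and an inference that does not follow from it. The 12.4-point margin is the half-width of a two-sided 90% interval, or equivalently a one-sided 95% bound. The labels attached to it would give 9.7 and 14.8 points. As support for a two-sided statement that the difference is not zero, it carries 90% confidence.

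The practical size is the gap between 12.4 and 14.8 points. At two-sided 95% the planning interval clears zero by 0.2 points rather than 2.6, and it covers zero in the 10% stress case. An observed reduction between about 12.4 and 14.8 points would exclude zero under one reading and not under the other (taking the planning standard error).

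These figures assume the planning rates, equal arms of 75, a normal-approximation interval, and an observed difference exactly equal to the planning difference. They do not show that the sample size or the choice of analysis is wrong.

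**What to change.** State which level is intended and make the sentences agree with it. Either option repairs the text, and the choice is the sponsor's:

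- **(a) One-sided 95%.** Relabel the figure as a two-sided 90% confidence interval (equivalently a one-sided 95% bound) with half-width 12.4 points. Reword the conclusion as one-sided 95% confidence in a reduction, not confidence that the difference is non-zero.
- **(b) Two-sided 95%.** Replace 12.4 with 14.8 points. Say that at the planning difference the interval is −29.8 to −0.2, so zero is only just excluded, and that it would be included with 10% missing outcomes (half-width about 15.6).

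Under either option, delete the stated equivalence of one-sided 90% with two-sided 95%, and report the primary interval at the chosen level. The sentence on the effect of 10% missing data needs no change.

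The cost is wording only. Neither option requires a new sample size or a different method; option (b) replaces the published precision with a less favourable figure. The choice is best recorded before outcome data are seen, since it fixes the level at which the primary interval is read.

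### A 12.4-point margin of error does not give sufficient power for a 15-point difference: with 75 per arm, power is about 63% (one-sided 5%) or 51% (two-sided 5%) at the planned rates

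*Protocol article*

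**What the plan says.** All of this is in the Statistical analysis section of the protocol article, except the allocation ratio, which is in the Design section.

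- **Basis of the sample size.** The aim is to estimate the difference in event rates with a controlled interval width. No target power is given.
- **Size.** The plan is for "a sample size of 150 participants (75 in each arm"), consistent with the Design section, which will "assign participants in a 1:1 ratio".
- **Assumed effect.** The calculation supposes that "acute adverse events are reduced from 40% to 25% (absolute rate difference of −15" points).
- **Precision.** This is said to yield a "one-sided 90% confidence interval (one-sided equivalent to 95% confidence interval for a two-sided test) with 12.4% margin of error".
- **First inference.** "Thus, we expect to have >95% confidence that the true rate difference is non-zero".
- **Second inference.** The sentence beginning "If adverse event rates in the standard arm were higher or lower than expected (30–70"%) concludes that "we would still have sufficient power to detect the assumed 15% absolute rate difference".
- **Missing data.** The section adds that "even 10% missing data would have a minimal impact on the margin of error (<1"%).

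**The concern.** Half-width and power are different quantities. The half-width says how far the interval extends on each side of the observed difference. Power is the chance that the observed difference lands far enough from zero for the interval to exclude it. If the true difference is 15 points, the observed one falls short of 15 about half the time. A margin somewhat below 15 therefore gives a power somewhat above 50%, and no more than that.

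The text moves from the first quantity to the second without a calculation, and extends the conclusion to standard-arm rates where the variance is mostly larger than at 40%. What is at stake is how the result is read. The closing paragraph of the Summary makes a phase III trial the next step if the hypothesis is confirmed. A reader told that power is sufficient and confidence exceeds 95% will give a non-significant result more weight than the design supports.

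**Working it through.** **Inputs (protocol article).** n = 75 per arm; 40% versus 25%; margin 12.4 points; standard-arm range 30 to 70% with a 15-point difference throughout; 10% missing data.

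**1. Reproduce the margin.**
SE = √(0.40×0.60/75 + 0.25×0.75/75) = √(0.4275/75) = 0.0755.

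| Multiplier | Meaning | Half-width |
|---|---|---|
| 1.282 | true one-sided 90% bound | 9.7 points |
| 1.645 | two-sided 90% interval, i.e. one-sided 5% | 12.4 points |
| 1.960 | two-sided 95% interval | 14.8 points |

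The stated 12.4 is reproduced only with 1.645. It is neither a one-sided 90% bound nor a two-sided 95% half-width, so the label and its parenthesis do not describe the figure.

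**2. Reproduce the missing-data remark.** With 67.5 per arm, 1.645 × √(0.4275/67.5) = 13.1 points, an increase of 0.7. That statement is correct.

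**3. Power at the planned rates.** Power = Φ(0.15/SE − z), and 0.15/0.0755 = 1.987.
- One-sided 5%: Φ(1.987 − 1.645) = Φ(0.342) = 63%; miss probability 37%.
- Two-sided 5%: Φ(1.987 − 1.960) = Φ(0.027) = 51%; miss probability 49%.

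A pooled null variance gives 63% and 50%. Exact enumeration of the z-test gives 63% and 50%.

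**4. Power over the claimed range (unpooled, 15-point difference).**

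| Standard-arm rate | 90% half-width | 95% half-width | Power, one-sided 5% | Power, two-sided 5% |
|---|---|---|---|---|
| 30% | 11.0 | 13.2 | 72% | 61% |
| 40% | 12.4 | 14.8 | 63% | 51% |
| 50% | 13.1 | 15.6 | 59% | 47% |
| 57.5% | 13.3 | 15.8 | 58% | 46% |
| 70% | 12.9 | 15.3 | 61% | 48% |

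From 45% to 70%, power is below the 40% case at every rate computed, and the two-sided 95% half-width exceeds 15 points.

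**5. The 95% confidence sentence.** If the observed rates were exactly 40% and 25%, the two-sided 95% interval would run from 15 − 14.8 = 0.2 to 15 + 14.8 = 29.8 points and just exclude zero. That describes one outcome at the centre of the distribution. The probability of excluding zero before the data are seen is the 51% in step 3.

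**6. Fisher's exact test (the repeat analysis).** By enumeration at 40% versus 25%: 43% if two-sided, 56% if one-sided. The article does not state the sidedness.

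**7. Difference needed for 80% power, 75 per arm.** Solving d/SE(d) = z + 0.842:
- At a 40% standard-arm rate: 18.4 points (one-sided) or 20.4 points (two-sided).
- Over 30 to 70%: 16.4 to 19.9 points (one-sided) or 18.1 to 22.3 points (two-sided).

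**The case against.** The strongest reply is that this is a precision-based phase II trial with no power target, so the word sufficient has no fixed meaning and 80% is an outside benchmark. The figures that size the trial reproduce. In the design's own terms, the 90% half-width stays between 11.0 and 13.3 points over the whole range, always below 15, and the sentence can be read as a loose way of saying so.

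Part of this stands. The design basis is legitimate, and nothing in the article obliges the trial to reach 80%. A reader might infer that the trial is too small and must grow; 80% power at 40% versus 25% would take 120 per arm one-sided or 152 two-sided. The article does not support that inference, because it sets no such target.

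The reply does not rescue the sentence. The article itself uses the word power, in a statement about detecting a difference, and plans significance tests. A half-width below 15 points secures only power above 50%. The most lenient reading, one-sided 10%, gives 72 to 83%, reaches 80% only near a 30% standard-arm rate, and contradicts the 12.4-point margin.

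Three other strong readings should be resisted:
- That a 12.4-point margin makes the result close to a coin toss. That describes two-sided 5%; at the level matching 12.4 points, power is 63%.
- That the 43% for Fisher's exact test is the power of the primary analysis. The primary test is a stratified Cochran–Mantel–Haenszel test, and the 43% also assumes a two-sided test.
- That an interval including zero will be taken as evidence against tumor-focused treatment. The article does not say so; it says only what follows if the hypothesis is confirmed.

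**Conclusion.** The two claims are wrong as written. At the planned rates the probability of excluding zero is about 63% (one-sided 5%) or 51% (two-sided 5%). Over standard-arm rates of 30 to 70% it is 58 to 72% or 46 to 61%. No 5% reading reaches 80% anywhere in that range.

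These figures rest on 75 analysed per arm, a true 15-point difference and an unstratified normal approximation. Power for the stratified test was not computed. Ten percent missing data lowers the planned-rate figures to about 59% and 46% (pooled variance). Both levels are shown because the interval label leaves the sidedness unclear, although the 12.4-point margin matches one-sided 5%.

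The fault lies in what is claimed for the design. The choice of a precision-based design and the sample size are not in question. It should be fixed, but it does not put the conduct of the trial in doubt.

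**What to change.** 1. Delete the sentence on more than 95% confidence and the sentence on sufficient power.
2. Correct the interval label: 12.4 points is the half-width of a two-sided 90% interval, equivalent to one-sided 5%; the two-sided 95% half-width is 14.8 points. Say which one governs the primary comparison.
3. Insert wording such as: *With 75 per arm and rates of 40% and 25%, the probability that the interval excludes zero is about 63% at one-sided 5% and 51% at two-sided 5%; over standard-arm rates of 30 to 70% with a 15-point difference it is 58 to 72% and 46 to 61%. At a 40% standard-arm rate, 80% power requires a difference of about 18.4 points (one-sided) or 20.4 points (two-sided); over 30 to 70% the required differences are 16.4 to 19.9 and 18.1 to 22.3 points.*
4. Keep the precision-based design and the 150 participants.

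The cost is wording only, with a less favourable figure on the page. No additional participants and no change to the analysis are needed.
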